# Objective and purpose

| **Objectives** | **Outcome Measures/Endpoints** |
| --- | --- |
| **Primary Objective** | To determine the kinetics (rate of change) of SARS-CoV-2 specific protein antibody titres in proven cases of SARS-CoV-2 over the 6 month period following infection. |
| **Secondary Objectives** | 1. To determine the proportion of completely asymptomatic healthcare workers who have evidence of SARS-CoV-2 antibodies in their serum indicative of past infection 2. To determine the attack rate of SARS-CoV-2 in healthcare workers who have antibodies versus those who do not have antibodies 3. To determine the immune correlates of protection (antibody titres sufficient for protection) against future exposure to SARS-CoV-2 4. To investigate the roles of T-cell function and IgA in those with seropositivity to SARS-CoV-2. 5. To examine key risk factors influencing susceptibility to SARS-CoV-2. These include social determinants of health, such as housing, work and transport in the urban setting. 6. To ascertain clinical manifestations of COVID-19 disease and long term consequences of disease. 7. To pool international data in standardized form across hospital sites for longitudinal comparative review of risk factors and health service impact. 8. To assess the impact of COVID-19 on health worker staffing in hospitals and inform strategies for future planning. 9. To review antibody responses to vaccination against SARS-CoV-2 following it’s availability and analyse subsequent infection rates. |

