Within this initial planned cohort (**Study Flow Diagram 1, page 18**), a subset of ~400 staff members with confirmed symptomatic, PCR positive, antibody positive or equivocal, SARS-CoV-2 disease (and an additional 2100 staff sero-positive or equivocal staff members who were either PCR negative or asymptomatic) will be followed with intensive 1 to 2 monthly blood sampling to determine antibody titres to the SARS-CoV-2 specific protein using the *EDI^TM^* ELISA assay. Participants who are seropositive or equivocal will also have the option of providing an additional one off 20ml sample for T-cell assay analysis and a salivary sample for IgA analysis.

All 7000 recruited healthcare workers (2100 SARS-CoV-2 sero-positives and N~4900 seronegatives) will have blood taken for serological testing at baseline then at 6-monthly intervals for a total of 6 years. In addition to repeated serological testing, participants will continue as all healthcare workers at GOSH to have access to the staff testing program. This program tests symptomatic staff members by nasal swab PCR testing for SARS-CoV-2. Staff who have been tested for SARS-CoV-2 through the staff testing program will be consented for the PCR and serology results to be used in the study. All participants will also be asked to complete a detailed health and demographic questionnaire prior to each appointment, electronically. The technology design of the questionnaire will optimise participation. If key questions are missed, participants will be contacted by phone, text or email to optimise data collection and statistical analysis. As key factors impacting COVID-19 evolve, questions on review questionnaires will address these.

The data will enable us to determine the attack rate (percentage of healthcare workers with PCR proven infections/re-infections) and incidence (the rate of occurrence of disease) of SARS-CoV-2 infection amongst healthcare workers with and without antibodies. The comparison of the attack rate will indicate the protection antibodies provide. Further, the stratification of results by antibody titres, will provide information on whether a specific level of antibody confers protection.

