## Discontinuation/Withdrawal of Participants from Study

Although we anticipate a high uptake, engagement and retention with the study due to the common first hand experience with SARS-CoV-2, participants may withdraw from the study at any stage. The information sheet clearly states the email addresses of the study investigators that can be contacted should the participant wish to withdraw from the study. No further procedures or observations will be required. Participants will have the option of leaving the study but allowing data to be kept and samples stored for research OR leaving the study, erasing all data and destroying all samples. A note will be made on the study record and the "last successful follow-up" date will be taken as the "lost to follow-up/left the study" date for the purposes of statistical analysis. Whilst the data from previous questionnaires is still able to be identified, if the study participant requests that all their data be erased or removed from the database, it will be excluded from analysis.

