# Statistics

## Statistical methods to be employed (plan of analysis)

Antibody titres are expected to follow a negative exponential (log-linear) decay over time as seen following other respiratory viral infections. Serial antibody titres will be log-transformed and then multivariate linear regression models will be used to determine the predictors of antibody decay. Variable attack-rate between groups will be compared with a two-sample test of proportions and the incidence of COVID-19 disease between study groups will be compared using survival analysis with log-rank testing.

Fig.1: An estimated sample size of 4500-8000 total participants (with seropositive sample size of 1500-2700 participants, Fig.1, x-axis) provides 80% power at alpha 0.05 to detect an effect size of ≥17% decline in antibody titres over 12-months. This is based on a seropositivity prevalence of 33%, as observed in preliminary results so far and a negative exponential (log-linear) model of waning antibody titres, with 3 co-variate predictors of antibody decay, including sex, age and ethnicity (green line) or 4 co-variate predictors, including sex, age, ethnicity and co-morbidities (blue line). For comparison, the model was repeated based on 20% decline in baseline antibody titres over 12-months (using alpha 0.05), with the same 3 (orange line) or 4 (red line) co-variate predictors of antibody decline.

[figure not shown]

In order to determine the study power for varying effect sizes with unequal group sizes we undertook a two-sample power calculation of proportions with group sizes of 2100 seropositive cases and 4900 seronegative comparators using R (foundation for statistical computing) pwr function pwr.2p2n.test (Figure 2).

Figure 2. Power curve for group sizes of 2100 and 4900 participants showing that this study will have the power to detect an effect size of 0.07 i.e. a difference in the proportion in the attack rate between the two groups of 7%.

[figure not shown]

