We will also undertake an exploratory analysis using survival analysis to compare the hazards of infection in both groups over the course of the study using the date of reported and PCR proven SARS-CoV-2 infection as an event and the last follow up date or the final interview as the censorship date. We anticipate a high retainment rate in the study for three reasons a) GOSH has high baseline staff retention rates b) hospital staff already understand the rationale and the importance of this research and c) we have already received high levels of interest and engagement with the study.

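### The serostatus comparison meant to show protection is a crude proportion with no time horizon, biased if follow-up differs by serostatus, while the censored survival comparison appears to be only exploratory

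*Protocol*

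**What the plan says.** The protocol's Objective and purpose table gives secondary objective 2 as "To determine the attack rate of SARS-CoV-2 in healthcare workers who have antibodies versus those who do not have antibodies". Section 7.1 (Description of study design) defines the measure as "attack rate (percentage of healthcare workers with PCR proven infections/re-infections", with no time horizon and no person-time, and adds: "The comparison of the attack rate will indicate the protection antibodies provide". The same section separately defines incidence as a rate of occurrence.

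Section 12.1 assigns a test to each quantity: "Variable attack-rate between groups will be compared with a two-sample test of proportions and the incidence of COVID-19 disease between study groups will be" compared by a log-rank test. The power calculation for the serostatus contrast (Figure 2) is a two-sample calculation of proportions with 2100 and 4900 participants. The section then closes with: "We will also undertake an exploratory analysis using survival analysis to compare the hazards of infection in both groups over the course of the study". The censoring date (last follow-up or final interview) is attached to that exploratory analysis.

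Section 9.7 says that for people who leave, the last successful follow-up "date will be taken as the 'lost to follow-up/left the study' date for the purposes of statistical analysis". Section 9.5 has seropositive staff seen every 1 to 2 months in an initial intensive phase and seronegative staff every 6 months. After that phase everyone is seen 6-monthly for the 6-year study.

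**The concern.** The objective's wording, the sentence in section 7.1 about protection and the power calculation all point to the crude percentage as the measure that answers objective 2. Taken over everyone enrolled, that percentage counts a person followed for 6 months the same as one followed for 6 years. A group that stays longer has more time in which an infection can be recorded, so it shows the higher attack rate even when the infection hazard is the same in both groups.

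If seropositive staff leave sooner, for instance because of their heavier early schedule, antibodies look protective when they are not. If seronegative staff leave sooner, antibodies look harmful, or real protection is masked. The planned method that removes this effect is a censored survival comparison, and section 12.1 appears to rank it as exploratory.

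**Working it through.** **Inputs from the protocol.** Groups of 2100 and 4900; 6 years of follow-up; attack rate as a plain percentage. **Assumed, because the protocol gives no figure:** infection hazard of 5% or 2% per year; loss of 5% to 15% per year; exponential infection and drop-out times, with drop-out unrelated to infection risk; everyone enrolled in the denominator.

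**1. The plan's own figure.** 2100 × 4900 / 7000 = 1470. At 80% power and two-sided 5% (stated for Figure 1, assumed for Figure 2) the detectable effect size is (1.960 + 0.842) / √1470 = 0.0731, which agrees with the stated 0.07 after rounding. The calculation therefore uses the full enrolled numbers, with no horizon and no drop-out.

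**2. Expected crude attack rate.** With hazard λ and loss rate δ, the probability that an infection is observed within 6 years is λ/(λ+δ) × (1 − exp(−6(λ+δ))).

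- λ = 0.05, δ = 0.05: 0.5 × (1 − e^−0.6) = 0.2256
- λ = 0.05, δ = 0.10: 0.3333 × (1 − e^−0.9) = 0.1978

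The hazard is identical, yet the crude rates differ by 0.0278.

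**3. False-positive rate of the proportions test.** With seropositive loss 5% and seronegative loss 10%, the pooled proportion is (2100 × 0.2256 + 4900 × 0.1978) / 7000 = 0.2061. The standard error is 0.01055 pooled and 0.01075 unpooled. The rejection probability is Φ((0.0278 − 1.96 × 0.01055) / 0.01075) = 74.6%. The last two columns are from simulation, 1500 runs per setting.

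| Infection per year | Loss per year, seropositive vs seronegative | Crude attack rate | Proportions test, formula | Proportions test, simulated | Log-rank, simulated |
|---|---|---|---|---|---|
| 5% | 5% vs 5% | 22.6% vs 22.6% | 5.0% | 5.4% | 4.7% |
| 5% | 5% vs 7% | 22.6% vs 21.4% | 19.6% | 18.5% | 4.7% |
| 5% | 5% vs 10% | 22.6% vs 19.8% | 74.6% | 73.5% | 5.5% |
| 5% | 10% vs 15% | 19.8% vs 17.5% | 63.0% | 62.9% | 4.7% |
| 2% | 5% vs 5% | 9.8% vs 9.8% | 5.0% | 4.9% | 4.9% |
| 2% | 5% vs 7% | 9.8% vs 9.3% | 10.9% | 11.1% | 5.6% |
| 2% | 5% vs 10% | 9.8% vs 8.6% | 39.0% | 37.3% | 5.0% |
| 2% | 10% vs 15% | 8.6% vs 7.5% | 31.7% | 30.5% | 4.5% |

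With seropositive staff staying longer, the spurious result is harm. Swapping the losses turns it into spurious protection at nearly the same rate (about 74% for 10% vs 5% at 5% infection per year).

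**4. Loss that differs only early.** Take 5% loss per year in both groups, plus an extra 5% or 10% of seropositive staff lost at 6 months. Infection observed by 6 months is 0.5 × (1 − e^−0.05) = 0.0244. The seropositive attack rate becomes 0.95 × 0.2256 + 0.05 × 0.0244 = 0.2155, or 0.90 × 0.2256 + 0.10 × 0.0244 = 0.2055. Step 3 then gives false-positive rates of about 15% and 46% at 5% infection per year.

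**5. When there is a true effect.** Simulation with 600 runs per setting, 5% infection per year in seronegatives, and loss entered as an annual probability (slightly larger than the same figure used as a rate):

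- Hazard ratio 0.8, loss 5% seropositive vs 10% seronegative: protection found by the proportions test in 17% of runs and by log-rank in 96%.
- Hazard ratio 0.8, loss 5% vs 15%: the two tests are significant in opposite directions in 30% of runs.
- Hazard ratio 0.8, equal loss of 5%: the two tests differ in significance in under 1% of runs.
- Hazard ratio 0.5: the tests disagree in at most 4% of runs across the infection rates tried.

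**The case against.** **Two quantities, two tests.** Section 7.1 distinguishes attack rate from incidence, and section 12.1 gives each its own test. That is coherent, and reporting both is not an error. A reader might infer that two rival tests compete to decide objective 2. The text does not support that: it points to the proportions test, though no sentence ranks the two. This makes the choice of that test matter more.

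**Is the exploratory analysis the log-rank test?** A reader might take it as certain that the protocol downgrades its own log-rank test. The closing paragraph of section 12.1 does not mention log-rank, and the word *also* could introduce a further hazard analysis. The same analysis is the likelier reading, but not a certain one.

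**Schedules differ only at first.** This is correct, and a loss difference sustained for 6 years does not follow from it. Step 4 shows that a purely early difference is enough to matter.

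**Loss rates are assumed.** They are. Losses of 5% vs 7%, 5% vs 10% and 10% vs 15% per year imply about 26% vs 34%, 26% vs 45% and 45% vs 59% gone by 6 years. Section 12.1 expects high retention, and staff who leave the trust may stay in the study. Neither statement gives a figure or addresses balance between the groups.

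**A proportion could be taken at a fixed horizon among those followed that long.** It could, and a statistical analysis plan might say so. It would be wrong to claim that no test of proportions can use the follow-up dates. But the protocol's definition, test and power calculation contain no horizon, and it already plans a method that uses all the follow-up.

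**Conclusion.** The point stands as a weakness in a stated choice of analysis for a secondary objective. The measure said to indicate protection is a crude proportion that is biased whenever follow-up differs by serostatus, while the comparison that handles censoring is a planned method in one paragraph of section 12.1 and, probably, exploratory in the next.

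With no true effect and assumed losses of 5% vs 7% up to 5% vs 10% per year, the proportions test rejects in about 20-75% of studies at 5% infection per year and 11-39% at 2%, against about 5% for log-rank. The log-rank figure holds for drop-out unrelated to infection risk.

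A reader might infer that the two tests will reach opposite conclusions. That needs unequal follow-up together with a null or modest effect. With equal losses both hold their 5% level, and with a strong effect they almost always agree. The protocol does not show that follow-up will be unequal; it gives no basis for assuming that it will be equal.

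**What to change.** In section 12.1, reconcile the two statements on survival analysis. Make time to first infection during follow-up, censored at the dates already defined, the main analysis for objective 2: a log-rank test with a hazard ratio and 95% confidence interval. Report attack rate by serostatus as Kaplan-Meier cumulative incidence at stated times, in place of the crude two-sample test of proportions. If a further hazard analysis is meant to stay exploratory, say how it differs from the log-rank comparison.

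The cost is wording plus a new power statement, since the analysis and the dates are already planned. Power should be given in events. With a 30:70 split, two-sided 5% and 80% power, the number needed is (1.960 + 0.842)² / (0.3 × 0.7 × (ln HR)²): 78 events for a hazard ratio of 0.5, 294 for 0.7 and 751 for 0.8. The protocol states no infection rate or event count to set against these, so one would have to be assumed and stated.

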## Baseline Assessments

Baseline assessments will include the completion of a standardized questionnaire (Appendix D: Study Standardized Questionnaire) followed by an appointment for a blood test to be taken by trained study staff. At this appointment we will take 4ml of blood for serological testing and 4ml of EDTA blood for storage and future research.

We have amended the online survey to include details about other emerging SARS-CoV-2 risk factors including medical conditions, ethinic background (BAME), home occupancy and ability to distance in the workplace. We have also added a second email address box that allows to follow up staff once they have left the trust, we have expanded the previous testing history to include additional information about home testing kits and other ELISA tests. Severe disease markers and complications of COVID-19 are also included and vaccination history is also included to prepare for when vaccination is rolled out.

Questionnaire development will utilise technology similar to other NHS staff surveys that allow completion on personal mobile devices. The questionnaire interface would be separated from the database, so they can employ different levels and methods of security. Many hosting services have built-in defences like firewalls, access logs, and authorisation protocols to restrict access, and the stored data should also be encrypted using a strong algorithm. Any data transferred to the database, e.g. via the interface, should also be encrypted to ensure that it is unreadable to anyone who intercepts it. If the database is a SQL database, the interface must also employ defences against "SQL injection" attacks, to prevent any code entered into forms doing any damage or exposing the data.
Regularly migrating identifiable information to internal servers (perhaps while leaving some anonymised statistical data if this is required) would also significantly reduce the risk of data theft.

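### Protection by antibodies is to be judged from unadjusted comparisons of seropositive and seronegative staff, so any persisting difference in exposure biases it toward, or past, no protection

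*Protocol*

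**What the plan says.** Secondary objective 2 compares the attack rate in healthcare workers with and without antibodies. For it, section 12.1 of the protocol (Statistical methods to be employed) states that "Variable attack-rate between groups will be compared with a two-sample test of proportions" and that "the incidence of COVID-19 disease between study groups will be compared using survival analysis with log-rank testing". It later adds an "exploratory analysis using survival analysis to compare the hazards of infection in both groups over the course of the study". No covariate or stratum is named for any of the three.

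The only model with several predictors in that section concerns titres: "multivariate linear regression models will be used to determine the predictors of antibody decay".

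Section 7.1 (Description of study design) gives the reading: "The comparison of the attack rate will indicate the protection antibodies provide". The one stratification it mentions is by titre: "the stratification of results by antibody titres, will provide information on whether a specific level of antibody confers protection".

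Secondary objective 5 sets out to examine risk factors for infection, among them housing, work and transport. Section 9.4 (Baseline Assessments) adds questionnaire items on "home occupancy and ability to distance in the workplace". Section 13.1 (Source Documents) says new recruits are asked about exposure to SARS-CoV-2. Nowhere are these data tied to the protection comparison.

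**The concern.** A positive baseline antibody test is the result of earlier infection. Whatever made infection more likely before enrolment is therefore over-represented among seropositive staff. If it continues afterwards, because someone still works in the same unit, lives in the same household or travels the same way, the seropositive group enters follow-up facing a higher force of infection. A crude comparison then combines two opposing effects: protection by antibodies, and the greater exposure of those who have them.

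This is confounding. Updating serostatus at each visit or handling person-time correctly would not remove it. The error matters most when protection is partial, which is plausible here because follow-up lasts six years and titre decay is the primary objective. The study could report little or no protection, or excess risk in antibody-positive staff, because of where those staff work and live.

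**Working it through.** **1. The plan's own figure.** With 2100 and 4900 participants, two-sided alpha 0.05 and 80% power (assumed, because the text gives neither for Figure 2), the detectable effect on the arcsine scale of pwr.2p2n.test is

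h = (1.960 + 0.842) × √(1/2100 + 1/4900) = 2.802 × 0.02608 = 0.073.

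This agrees with the stated 0.07 to rounding. The group sizes are as planned, and the calculation allows for no confounding.

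**2. Inputs for the bias.** From the protocol: 2100 seropositive and 4900 seronegative, so 30% seropositive. Assumed, because the protocol gives no values: half of staff are high-exposure; the seronegative attack rate is 10%; the exposure hazard ratio R is 1.5, 2 or 3 and is the same in the first wave and in follow-up.

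**3. Who is seropositive.** Solve for the first-wave cumulative hazard H in low-exposure staff:

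0.5(1 − e^(−H)) + 0.5(1 − e^(−RH)) = 0.30.

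For R = 3, H = 0.187, so 42.9% of high-exposure and 17.1% of low-exposure staff were infected. The high-exposure share is 0.5 × 0.429/0.30 = 72% of seropositives (call it s₁) and 0.5 × 0.571/0.70 = 41% of seronegatives (s₀).

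**4. Crude attack rates.** Find the follow-up hazard L from s₀(1 − e^(−RL)) + (1 − s₀)(1 − e^(−L)) = 0.10. With true hazard ratio θ for antibodies, the seropositive attack rate is

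A₁ = s₁(1 − e^(−RLθ)) + (1 − s₁)(1 − e^(−Lθ)).

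For R = 3, L = 0.059. At θ = 0.7, A₁ = 0.716 × 0.1165 + 0.284 × 0.0405 = 0.095. Apparent protection is 1 − A₁/0.10.

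**5. Power.** Two-sided two-proportion test with pooled variance under the null: Φ((|A₁ − 0.10| − 1.96·SE₀)/SE₁), where SE₀ is the pooled and SE₁ the unpooled standard error.

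| R, fully persistent | High-exposure share, seropositive / seronegative | No protection (θ = 1): A₁, apparent excess | 30% protection (θ = 0.7): A₁, apparent protection | Power at θ = 0.7 | 80% protection (θ = 0.2) appears as |
|---|---|---|---|---|---|
| 1.5 | 58% / 46% | 10.5%, 5% | 7.5%, about 25% | 93% | 78% |
| 2 | 64% / 44% | 11.3%, 13% | 8.1%, 19% | 72% | 76% |
| 3 | 72% / 41% | 13.2%, 32% | 9.5%, 5% | 10% | 72% |

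Without confounding, θ = 0.7 gives A₁ = 1 − 0.9^0.7 = 7.1%, an apparent protection of 29% with 98% power. The one-point gap from 30% is the difference between a hazard ratio and a risk ratio, not bias. With no true protection, the chance of a significant result in the direction of harm is 9%, 39% or 97%, against a nominal 2.5%.

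**6. When the sign changes.** From the excess risks, 1 − 1/1.046, 1 − 1/1.133 and 1 − 1/1.323 give 4%, 12% and 24%. Real protection smaller than this appears as harm. Solving for θ directly gives 5%, 12% and 26% on the hazard scale.

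**7. Sensitivity.** If the excess gradient halves in follow-up, 30% protection appears as 23% with power 88% (R falling from 2 to 1.5) or as 14% with power 43% (from 3 to 2). If the gradient vanishes, so does the bias. With 20% rather than 50% high-exposure staff and full persistence, no protection appears as 4%, 12% or 35% excess.

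**The case against.** The strongest reply is that this belongs to a statistical analysis plan. The comparison serves a secondary objective, section 12.1 describes it in two short clauses, and the exploratory hazard comparison names no model, so an adjusted one would be compatible with it. Adjustment is indeed not excluded. But the protocol does not leave the method open. It names unadjusted tests, computes power for a two-proportion test and says in section 7.1 how the result will be read. That combination is fixed, and followed as written it would be biased.

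Second, greater exposure of seropositive staff is inferred, not stated. Objective 5 proposes to examine risk factors and does not establish them. The Population section describes frontline workers representative of all departments, which may narrow the occupational gradient, although section 9.3 also admits staff with no exposure. Full persistence of the gradient is a further assumption, and the result depends heavily on it. These points stand: the direction follows if the factors matter and last, but the size is unknown.

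Third, a reader might infer that the questionnaire records the relevant exposures before every appointment, so that adjustment needs no new data. The protocol does not confirm this. Distancing and home occupancy are listed under Baseline Assessments, section 7.1 promises a health and demographic questionnaire before each appointment, and section 9.5 speaks of repeating a symptom questionnaire. The form itself is not visible in the text reviewed.

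**Conclusion.** The point holds in conditional form. The protocol fixes unadjusted comparisons for objective 2 and gives the attack-rate comparison a causal reading. If the exposure factors it sets out to study drive infection and persist, estimated protection is too low. Under the stated assumptions the distortion is small at a gradient of 1.5, material at 2 and close to complete for 30% protection at 3. It is roughly halved if the excess gradient halves in follow-up.

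A reader might go further and infer that the analysis will reverse real protection. The figures support that only for weak protection, below about 4%, 12% or 24% at gradients of 1.5, 2 and 3. Protection of 80% would remain plain. Nor do the documents show that seropositive staff are in fact more exposed, so none of these figures predicts what the study will find.

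**What to change.** In section 12.1, name as the protection analysis for objective 2 a hazard or rate model adjusted for, or stratified by, exposure. Use at least staff group or department, ability to distance and home occupancy from baseline, updated where follow-up questionnaires repeat them. Check against the questionnaire that staff group or department is recorded. Keep the crude proportions and the log-rank test as descriptive results. Reword section 7.1 so that the adjusted comparison, not the crude attack-rate difference, is what indicates protection. Choices about the time scale and delayed entry address other problems and are not needed for this one.

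The cost is wording and a somewhat more complex model. Baseline adjustment should need little or no new collection; adjustment updated over follow-up may need the items added to later questionnaires. A little precision is lost, and only measured exposure is controlled, so the report should say that residual confounding remains possible.

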# Subject Withdrawal Criteria

The choice of whether to withdraw from the study is dependent on the participant. As clearly explained in the information sheet they are free to withdraw from the study at any time. For those that withdraw from the study they may choose to a) leave the study but leave all their data and samples in order to contribute to the research project or b) erase the data and destroy the samples. In the latter case clearly these participants will not be able to be considered in the final analysis. If participants choose to leave the study, but agree to the usage of their data up until the point of leaving we will consider them "lost to follow-up" at their final successful follow-up interview and serological test. We currently do not have the resources to replace subjects that withdraw from the study but should funding support be obtained we would then do so. Equally should funding allow support to recruit more patients to improve the power and reduce the detectable effect size we will do so. If full funding is obtained for the project we will aim to scale up recruit all staff members at the trust.

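### Figure 2's attack-rate power uses the starting groups of 2100 and 4900 with no allowance for loss; on the scale the calculation uses, power at 0.07 is 76.5% before any loss and lower after it

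*Protocol*

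**What the plan says.** Section 12.1 plans a two-sample test of proportions for the attack rate (secondary objective 2). Its power calculation uses R's pwr.2p2n.test with "group sizes of 2100 seropositive cases and 4900 seronegative comparators". The Figure 2 caption states that "this study will have the power to detect an effect size of 0.07", and explains this as "a difference in the proportion in the attack rate between the two groups of 7" per cent. The text gives no alpha, sidedness or power level for Figure 2. The statement "provides 80% power at alpha 0.05 to detect an effect size of ≥17% decline in antibody titres over 12-months" belongs to Figure 1, the antibody-decay calculation.

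On loss, sections 9.7 and 11 let participants leave at any time. Those who choose erasure are excluded from analysis. Those who let their data stand are treated as lost at their last successful follow-up. Section 11 says: "We currently do not have the resources to replace subjects that withdraw from the study", and makes replacement conditional on new funding. Section 12.1 adds "We anticipate a high retainment rate in the study" and gives three reasons, but no rate. Section 8 keeps staff who leave the trust eligible for follow-up.

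**The concern.** The Figure 2 statement is unconditional, but it is calculated as if every enrolled person contributed a full outcome. The protocol itself provides for withdrawal, including withdrawal that removes all data, over a 6-year follow-up. Retention is argued only in words and no figure enters the calculation. Section 16 adds that funding covers baseline testing of the first 1000-1250 staff and that funding for follow-up is still being sought, so neither follow-up nor replacement is secured.

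What is at stake is the stated sensitivity of the comparison between staff with and without antibodies. A two-sample test of proportions makes no adjustment for incomplete follow-up. The log-rank analysis also planned in section 12.1 does handle censoring, but Figure 2 was not calculated for it.

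**Working it through.** **Inputs.** From section 12.1: n1 = 2100, n2 = 4900, effect size 0.07, function pwr.2p2n.test. That function takes Cohen's h = 2·arcsin√p1 − 2·arcsin√p2. Assumed, because the text does not state it for Figure 2: two-sided alpha 0.05. Also assumed, because the protocol gives no rate: loss L of 10%, 20% or 30%, equal in both groups.

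**Formula.** Power = Φ(h·s − 1.96), with s = √(n1·n2/(n1+n2)); the opposite tail is negligible. The h detectable with 80% power is (1.960 + 0.842)/s.

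**Reproducing the plan's figure.** s = √(2100 × 4900/7000) = √1470 = 38.34. Detectable h at 80% power = 2.802/38.34 = 0.0731, which rounds to the stated 0.07. At exactly h = 0.07: 0.07 × 38.34 = 2.684; 2.684 − 1.960 = 0.724; Φ(0.724) = 76.5%. So 0.07 matches the no-loss calculation in h, to two decimals and on the assumption that 80% power was the target.

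**Case A: lost participants give no data.** Both groups shrink by the factor (1 − L), so s = √(1470(1 − L)).

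| Loss | n1 / n2 | s | Power at h = 0.07 | h for 80% power |
|---|---|---|---|---|
| 0% | 2100 / 4900 | 38.34 | 76.5% | 0.073 |
| 10% | 1890 / 4410 | 36.37 | 72.1% | 0.077 |
| 20% | 1680 / 3920 | 34.29 | 67.0% | 0.082 |
| 30% | 1470 / 3430 | 32.08 | 61.2% | 0.087 |

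**Case B: lost participants stay in the denominator with partial follow-up.** Assume a constant hazard, loss uniform in time and attack rates of 5-20%. With λ = −ln(1 − p), the observed risk is (1 − L)p + L[1 − (1 − e^(−λ))/λ].

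Example with L = 20%, where h = 0.07 separates 10.0% from 12.2%:
- p = 0.100: λ = 0.1054, bracket = 1 − 0.100/0.1054 = 0.0509, observed risk = 0.0800 + 0.0102 = 0.0902.
- p = 0.12196: λ = 0.1301, bracket = 0.0623, observed risk = 0.0976 + 0.0125 = 0.1100.
- Observed h is about 0.066, and with 2100 and 4900 power is about 72%.

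Over attack rates of 5-20%, power is about 74%, 72% and 69-70% at 10%, 20% and 30% loss.

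**The caption's 7% reading.** A 7-point difference gives its smallest h when centred on 50% (46.5% against 53.5%): h = 0.140. Power is then 99.97% with full groups and 99.8% at 20% loss, and it is higher at any other attack rate. Conversely, h = 0.07 is a difference of about 1.6 points from a 5% attack rate (5.0% to 6.6%) and 2.2 points from 10% (10.0% to 12.2%). The two halves of the caption therefore describe different effects.

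**The case against.** The strongest reply is that the caption itself explains 0.07 as a 7% difference, and for that difference loss of this size is immaterial. This stands as a limit on the point: nobody should infer that the study is underpowered for a 7-point difference. It does not rescue the figure as calculated, because the named function works in h and 0.07 agrees with the no-loss h.

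Other replies also narrow the point:
- A reader might infer from section 11 that withdrawals will never be replaced. The same sentence makes replacement conditional on funding, and the section goes on to foresee extra recruitment if money allows.
- A reader might take 67% as the power the study will have. The documents do not support that. The 20% is an assumption, the protocol expects high retention and keeps staff who leave the trust eligible, and 67% requires every lost participant to give no data. Only those asking for erasure give none; with partial follow-up the figure is about 72%.
- The 76.5% itself assumes a two-sided 0.05 test. One-sided, it would be 85.1%, falling to 77.5% in Case A at 20% loss. The curve is not available here, so any power level marked on it could not be checked.
- Section 7.1 gives the attack rate no time horizon and section 9.8 plans yearly analyses, so the calculation is not stated to rest on complete 6-year outcomes. An earlier analysis would see less loss.
- The synopsis and section 7.1 already call about 7000 a starting cohort, and log-rank testing is planned as well. True, but neither puts a loss allowance into Figure 2.

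**Conclusion.** The point holds in limited form. Figure 2's power is stated without condition on the full starting groups, and the protocol contains no allowance for loss. On the h scale at two-sided 0.05, power at 0.07 is already below 80% with no loss, so there is no margin to absorb any. At assumed losses of 10-30% it falls to between 74% and 61%, depending on the amount lost and on how much data lost participants contribute. The detectable h moves from 0.073 to no more than 0.087.

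The effect is modest and concerns a secondary objective. It is an omitted allowance in a stated design property; the calculation as run contains no arithmetic error. Equating h = 0.07 with a 7% difference is the larger defect in the same caption, and any restatement of power that leaves it in place would still mislead.

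**What to change.** In section 12.1:
- Say that 2100 and 4900 are enrolled numbers.
- State the alpha, sidedness and power level behind Figure 2.
- Restate power and detectable h at a named retention with a range, for example 90%, 80% and 70%, and say whether lost participants are taken to contribute no data or partial follow-up.
- Replace the 7% gloss with the percentage-point differences that h corresponds to at stated attack rates; h = 0.07 is about 1.6 points from 5% and 2.2 points from 10%.

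The cost is one recalculation and a few sentences, and the stated figure becomes slightly less favourable. No change to recruitment is needed.
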